**Methods:**

Twenty-six healthy participants will be recruited for this cross-sectional study. Participants will walk, skip and run, at speeds ranging between 0.56–3.6 m/s, and perform plyometric movement trials at each gravity level (1, 0.7, 0.5, 0.38, 0.27 and 0.16g) in a randomized order. Through the collection of state-of-the-art kinetics, kinematics, muscle activation and muscle-tendon behaviour, a musculoskeletal modelling framework will be used to estimate lower limb joint reaction forces via tracking simulations.

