#### Sample size

As to our knowledge there are no directly comparable published data, a sample size estimation was performed based on the results of a pilot study conducted at the L.O.O.P. GBF. During this pilot study, a single participant performed submaximal single-leg hopping at 2 Hz (using a metronome) for 30 seconds under five simulated gravity conditions (1, 0.5, 0.37, 0.25, 0.17g). For each session, peak vertical joint reaction forces were calculated for the hip, knee and ankle using the same simulation framework as described in this protocol (see *“Planned Data Analysis”)*.

Using this simulation framework, means and standard deviations of the peak vertical joint forces of the hip, knee and ankle were calculated and extracted for each gravity condition, which were used to calculate the Cohen’s *d* effect sizes based on the mean difference and pooled standard deviations [48]. These data were then used in an *a priori* power analysis to estimate a required sample size of 21 (S1 File) using G*Power (version 3.1.9) [49] with: t-test (matched pairs), α = 0.05, Power = 0.95, two-tailed. In order to ensure adequate data collection, we estimate a maximal data loss of 25%, therefore our sample size target will be 26 participants.

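### The 25% data-loss allowance is added to the required 21 instead of being divided out, so a target of 26 covers a loss of only 19.2%; the effect is minor

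*Protocol article*

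**What the plan says.** The Sample size section of the protocol article describes a "power analysis to estimate a required sample size of 21 (S1 File"). The settings for that calculation are given as "t-test (matched pairs), α = 0.05, Power = 0.95, two-tailed". The effect size comes from a pilot in one participant and is described as Cohen's *d* "effect sizes based on the mean difference and pooled standard deviations", but its value is not printed in the article; the section refers to S1 File, which is not at hand.

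The section then moves from 21 to the recruitment target in one step: "we estimate a maximal data loss of 25%, therefore our sample size target will be 26 participants". The abstract repeats the number: "Twenty-six healthy participants will be recruited for this cross-sectional study". Neither the Recruitment section nor the data collection section describes replacing participants whose data are lost.

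**The concern.** The sentence presents 26 as the consequence of two stated numbers, a requirement of 21 and a maximal loss of 25%. A reader takes it as an assurance that 21 usable participants will remain even if the loss reaches that maximum. The three numbers do not fit together. Adding 25% of the requirement is not the same as allowing for 25% of the recruits to be lost, because the loss is taken from the larger number.

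At stake is whether the target protects the number on which the stated power depends. This is the only place in the article where the sample size is justified, and the error can be seen by hand.

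**Working it through.** **Inputs.** From the Sample size section: required number 21, maximal loss 25%, target 26, matched-pairs t-test, two-sided α = 0.05, power 0.95. The effect size is not in the article, so it is treated below as an assumption with a range.

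**1. Reproducing the plan's figure.** Required number × (1 + loss) = 21 × 1.25 = 26.25, which rounds to 26. This gives the stated target, but only by rounding down; rounding up would give 27.

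**2. The allowance that a 25% loss needs.** Required number / (1 − loss) = 21 / 0.75 = 28. Check: 28 × 0.75 = 21.

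**3. What 26 recruits leave at the stated maximum.** 26 × 0.75 = 19.5. In whole participants:

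| Lost of 26 | Share lost | Remaining |
|---|---|---|
| 5 | 19.2% | 21 |
| 6 | 23.1% | 20 |
| 7 | 26.9% | 19 |

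The largest loss that stays within 25% is 6, leaving 20. The largest loss that keeps 21 is 5, or 19.2%.

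**4. What this costs in power.** For a paired t-test with n participants and standardised paired effect dz, power is the probability that a noncentral t variable with n − 1 degrees of freedom and noncentrality dz × √n falls outside ± the 97.5% point of the central t distribution. Assume that 21 is the smallest n with power of at least 0.95. Then dz lies between 0.828 (power exactly 0.95 at n = 21) and 0.850 (power exactly 0.95 at n = 20). Across that range:

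| Evaluable n | Power at dz 0.828 | Power at dz 0.850 |
|---|---|---|
| 19 | 0.926 | 0.939 |
| 20 | 0.939 | 0.950 |
| 21 | 0.950 | 0.959 |

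Against the nominal 0.95, the loss is between nothing and 1.1 points with 20 participants, and between 1.1 and 2.4 points with 19. Steps 1 to 3 do not depend on dz.

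**The case against.** Several points can be made for the sponsor.

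- **The allowance is a maximum, not an expected rate.** With a loss of up to 5 of 26, the required 21 remain and nothing is missed. This stands, and it limits the consequence. It does not make the sentence correct, because the sentence claims cover up to 25%.
- **Whole people cannot be split.** Read as a strict ceiling, 25% of 26 permits 6 losses and leaves 20, one short. On that same reading 27 recruits would be enough: 6 of 27 is 22.2%, which leaves 21, and a seventh loss would be 25.9%. This also stands. The gap can therefore be described as one or two recruits, but 26 falls short either way.
- **Data loss may not mean whole participants.** The data come from many trials and several sensors in one session, so losses may be partial and differ by movement. The article does not say which is meant. Partial loss would make the head-count less exact for any one analysis, but it does not turn 21 × 1.25 into the right allowance.
- **The 0.95 is itself nominal.** It refers to one paired t-test with an effect size from a single pilot participant, whereas the Planned statistical analysis section specifies repeated-measures ANOVAs with Bonferroni-corrected post-hoc tests. Shifts of one or two points in that figure would hardly change how a result is read. This stands and is a reason to grade the point low.

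A reader might infer that a 25% loss leaves only 19 participants and that the study is then materially underpowered. The article does not support this. Leaving 19 means losing 7 of 26, or 26.9%, which exceeds the stated maximum, and even 19 would give power of at least 0.926 under the assumed effect range.

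**Conclusion.** The point holds as a minor arithmetic error. The target of 26 results from multiplying by 1.25 and rounding down, where a 25% loss calls for division by 0.75 and a target of 28. At the stated maximum, the required 21 is not protected: 19.5 remain on paper and 20 in whole participants. The target covers a loss of at most 19.2%.

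This conclusion uses only the article's own figures, reads data loss as loss of participants, and takes it that lost participants are not replaced, since no replacement is described. The power cost, at most about 1 point with 20 participants and about 2 points with 19, is conditional on the back-solved effect range. It should not be read as a property of the plan, because the effect size in S1 File was not available for checking. Nor has the figure of 21 itself been verified.

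**What to change.** Choose one of two corrections.

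- **Keep 26 and correct the allowance.** Replace the 25% in the Sample size section with wording such as: *a target of 26 participants allows for up to 19% data loss (5 of 26 participants)*. This costs one sentence and leaves recruitment unchanged; the only concession is a less generous stated allowance.
- **Keep 25% and correct the target.** State 28 in the Sample size section and in the Methods paragraph of the abstract. This costs two further participants, each attending both the familiarisation and the data collection visit.

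If a power figure for fewer than 21 participants is added, compute it from the effect size in S1 File, not from the range assumed here.

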### Data collection procedure and experimental setup

Prior to participating in the Familiarisation Session and the Data Collection Session, and after having received written and supplementary oral explanation in addition to having been given the opportunity to ask any questions they might have, written informed consent of all volunteer participants will be collected.

#### T0 –Familiarisation session

To familiarize with the L.O.O.P. vertical body weight support system, participants will initially perform a walking trial at 1.11 m/s, a skipping trial at 1.94 m/s and a running trial at 3.06 m/s, in addition to plyometric movements (fifteen submaximal hops, five submaximal countermovement jumps, three drop-jumps/landings) at each pre-defined simulated gravity level, in a non-randomized, descending sequence (1, 0.7, 0.5, 0.38, 0.27, 0.16g; Fig 1).

**Fig 1 pone.0278051.g001:**
[figure not shown]
Schematic of the experimental setup and data collection procedure.

#### T1 –Data collection session

After placing all motion capture markers and sensors on the participant’s body (see *“Study Hardware”*), each participant will perform a short, pre-defined warm-up (five-minute walking at their preferred walking speed in 1g, fifteen submaximal ankle hops and five submaximal countermovement jumps in 1g).

Before the experimental dynamic trials, static motion capture calibration will be conducted with participants quietly standing on the instrumented treadmill centrally within the motion capture volume in a T-pose (arms outstretched horizontally) for five seconds. All participants will then be exposed to a randomised sequence of simulated gravities (1, 0.7, 0.5, 0.38, 0.27, 0.16g). For each gravity level, the conditions for the locomotion trials (i.e., walking, running and skipping) at various defined speeds (Table 1), and plyometric movement trials (i.e., maximal ankle hopping, maximum effort countermovement jumping, and drop-jumps/landings) will also be performed in a randomised order (Fig 1).

**Table 1 pone.0278051.t001:** Conditions of the locomotion trials.

*Locomotion Style*	Speed (m/s)						
	0.56	1.11	1.39	1.94	2.50	3.06	3.61
Walking	X	X	X				
Skipping				X	X		
Running			X	X	X	X	X

All locomotion trials (walking, running and skipping) at each gravity level will be performed for at least one minute in a randomized order at speeds previously shown (Table 1) to facilitate analysis of joint internal loads and muscle-tendon unit behaviour and in relation to the cost of transport curve as a function of speed and gravity [15, 16].

All plyometric movement trials will be performed in the gravity conditions in a randomized order:

Vertical hopping will be performed in a single ramp-up-ramp-down trial consisting of 30 consecutive hops ascending from very shallow (<5cm) to maximal jump height, and then descending back to starting target height. Audio feedback (i.e., increasing and decreasing pitch) guiding hopping height will be provided similar to that used in our pilot study on the verticalized treadmill facility [18].Three maximal effort vertical countermovement jumps separated by at least 10 seconds.Three drop-jumps/landings separated by at least 10 seconds.

Self-selected rest periods will be encouraged between trials to minimise fatigue, and any discomfort associated with wearing the harness.

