#### Ultrasonography

Real-time B-mode ultrasound using a linear array transducer placed in a custom-made cast and secured with elastic bandages will be positioned over both the m. gastrocnemius medialis mid-belly to determine fascicle length and pennation angles [28, 53], and over the myotendinous junction (MTJ) to determine tendon length [54, 55]. The ultrasound recordings will be time-synchronized with the other data acquisition systems through a TTL pulse passed through the auxiliary ECG channel. A semi-automated tracking algorithm (e.g., UltraTrack Software [56]) will be used to quantify the muscle fascicle length and pennation angles during the stance phase as previously used by our team [57, 58]. For the determination of tendon length, three markers are attached to the ultrasound transducer, enabling the transformation of the tracked fascicle insertion point close to the MTJ in the 2D ultrasound image into the global reference system. Additionally, the m. gastrocnemius medialis tendon length, fascicle length and pennation angle are determined while subjects are lying prone with the knee and ankle joints in anatomically neutral positions (knee fully extended, sole perpendicular to the tibia) and muscles are relaxed [53].

Table 3 provides a comprehensive overview of all equipment used for each part of the experimental sessions.

**Table 3 pone.0278051.t003:** Description of the needed equipment and time for each part of the experimental sessions.

	Familiarisation (*T*_*0*_*)*		Data Collection (*T*_*1*_*)*	
*Activity*—Equipment		Time (Hours)		Time (Hours)
*Laboratory preparation*				
Treadmill	X	0.50	X	0.50
L.O.O.P. Body Weight Support System	X	0.25	X	0.25
Ultrasonography System			X	0.50
EMG System			X	0.25
3D Motion Capture System			X	1.50
*Participant Preparation*				
Body Weight Support Harness	X	0.50	X	0.25
Ultrasonography Probe Placement			X	0.50
EMG Placement			X	0.50
Retroreflective Marker Placement			X	0.50
*Familiarisation Trials*				
L.O.O.P. Body Weight Support System	X	0.50		
*Calibration Trials*				
Ultrasonography System			X	0.25
EMG System			X	0.25
3D Motion Capture System			X	0.25
*Locomotion Trials*				
Treadmill			X	2.50 hours (Based on 1 min trial + 1 min rest + room for additional rest x 6 gravity levels)
L.O.O.P. Body Weight Support System			X	
Ultrasonography System			X	
EMG System			X	
3D Motion Capture System			X	
*Plyometric Trials*				

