Treadmill			X	2.50 hours (Based on 3 min trial + 3 min rest + room for additional rest x 6 gravity levels)
L.O.O.P. Body Weight Support System			X	
Ultrasonography System			X	
EMG System			X	
3D Motion Capture System			X	

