### Planned statistical analysis

Statistical significance will be assumed at p < 0.05. Normality of the data will be assessed via Kolmogorov-Smirnov testing complemented by visual inspection of QQ plots and histograms. Normally distributed data will be presented as mean (±SD), non-normally distributed data will be presented as median (±IQR).

The effect of high-fidelity simulated gravity (1, 0.7, 0.5, 0.38, 0.27 and 0.16g) upon lower limb internal kinetics (i.e., joint reaction forces) when walking, running, and skipping at speeds ranging between 0.53–3.6 m/s will be determined by a Two-Way Repeated Measures ANOVA with:

Independent variables: six simulated gravity conditions; 10 locomotion trials (see Table 1)Dependent variables: Joint reaction forces of the hip, knee, and ankle

The effect of high-fidelity simulated gravity (1, 0.7, 0.5, 0.38, 0.27 and 0.16g) upon lower limb internal kinetics (i.e., joint reaction forces) during candidate plyometric movement (i.e., maximal ankle hopping, maximal effort countermovement jumping, and drop-jumps/landings) will be determined by a One-Way Repeated Measures ANOVA with:

Independent variables: six simulated gravity conditionsDependent variables: Joint reaction forces of the hip, knee and ankle

In case the assumption of sphericity has been violated–i.e., Mauchly’s test statistic is significant (p<0.05)–the Geisser-Greenhouse correction will be used to determine the effect of the independent variables on the dependent variables. If a significant effect of the simulated gravity condition, the locomotion trial, or the interaction between simulated gravity condition and locomotion trial is found, Bonferroni corrected post-hoc t-tests will be employed.

Alternatively, if data has a non-normal distribution the non-parametric Friedman test with Dunn’s post-test will be used.

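### The gravity ANOVAs have no term for block position, and no balancing of gravity order is stated, so any drift over the session stays in the error of every gravity contrast

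*Protocol article*

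**What the plan says.** Under the T1 data collection session, the article states that "All participants will then be exposed to a randomised sequence of simulated gravities", namely 1, 0.7, 0.5, 0.38, 0.27 and 0.16g. Within each level, the locomotion and plyometric trials "will also be performed in a randomised order (Fig 1". Neither sentence says how the order is generated. Fig 1, to which the text refers, is not shown.

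Table 3 budgets the locomotion trials at "2.50 hours (Based on 1 min trial + 1 min rest + room for additional rest x 6 gravity levels" and the plyometric trials at "2.50 hours (Based on 3 min trial + 3 min rest + room for additional rest x 6 gravity levels", which is 5.0 hours in one visit. Fatigue is anticipated: "Self-selected rest periods will be encouraged between trials to minimise fatigue".

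The planned statistical analysis fixes two models:
- **Locomotion:** a two-way repeated-measures ANOVA with "Independent variables: six simulated gravity conditions; 10 locomotion trials (see Table 1".
- **Plyometrics:** a one-way repeated-measures ANOVA with "Independent variables: six simulated gravity conditions" and no other factor.

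Neither model contains position or period. The Friedman alternative has no such term either. Bonferroni-corrected t-tests follow a significant effect.

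**The concern.** Each participant meets all six gravity levels one after another, so each gravity value is measured at some position from 1 to 6. If joint reaction forces drift with position, through fatigue, harness discomfort or practice, each within-person gravity difference also carries the drift between the two positions.

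Randomisation makes that extra component average zero, but it does not remove it. Because the stated models do not use position, the component goes into the error term, although block order will be known for every participant. What is at stake is the precision of every gravity contrast, and most of all the Bonferroni-corrected pairwise ones.

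**Working it through.** **Inputs from the article.** Six gravity levels; 10 locomotion trials per level (Table 1); 2.50 h + 2.50 h of trial time (Table 3); a required sample of 21 from a matched-pairs t-test at two-sided alpha 0.05 and power 0.95; a target of 26.

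**Assumptions.** The article gives no drift and no SD of paired differences. I take linear drift of 1%, 2% or 3% per block and a paired-difference SD of 15% without drift.

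**1. The plan's own sample size.** The effect size is in a supplementary file that is not shown, so 21 cannot be confirmed directly. Solving the noncentral-t power function backwards, n = 21 is the answer for a standardised paired difference d_z from 0.828 up to 0.850. The figure is attainable. I use d_z = 0.828, which gives power 0.95 at n = 21.

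**2. Exposure.** Locomotion is 10 x 6 = 60 trials. At 1 min of trial plus 1 min of rest that is 2.0 h, of which about 1 h is movement. The rest of the 2.50 h is extra rest. The plyometric work per level is one 30-hop ramp, three countermovement jumps and three drop-jumps/landings.

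**3. Variance of the position difference.** Position is uniform on 1 to 6, with variance 35/12. Two levels in one random order have covariance −(35/12)/5 = −35/60. The difference therefore has variance 2 x 35/12 + 2 x 35/60 = 5.833 + 1.167 = 7.0 (SD 2.65 positions). Enumerating all 720 orders gives the same value.

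**4. Inflation of contrast variance.** The factor is 1 + 7 x drift² / SD².
- 1% per block: 7 x 0.01² / 0.15² = 0.031
- 2% per block: 7 x 0.02² / 0.15² = 0.124
- 3% per block: 7 x 0.03² / 0.15² = 0.280

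At 2%, 0.124 x 21 = 2.6, so the loss is worth two to three of the 21 required participants.

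**5. Effect on power, with d_z = 0.828 before drift.** The article does not give the size of the Bonferroni family; the columns marked 15 assume all 6 x 5 / 2 = 15 gravity pairs.

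| Drift per block | n = 21, alpha 0.05 | n = 26, alpha 0.05 | n = 21, Bonferroni 15 | n = 26, Bonferroni 15 |
|---|---|---|---|---|
| none | 0.950 | 0.982 | 0.673 | 0.820 |
| 1% | 0.944 | 0.979 | 0.654 | 0.805 |
| 2% | 0.925 | 0.969 | 0.601 | 0.758 |
| 3% | 0.890 | 0.948 | 0.523 | 0.682 |

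**6. Validity.** In simulation with unrestricted random order, n = 26 and total drift over the session equal to one paired-difference SD (the 3% case, since 5 x 3% = 15%), the type I error was 0.049. The test keeps its level.

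**7. Cost of adjustment.** A six-level position factor takes 5 error degrees of freedom: in the one-way model at n = 26, from 25 x 5 = 125 to 120. The least-squares variance of gravity contrasts then rises as follows:
- Williams sequences: 0% at n = 24 or 30, and about 0.2% at n = 26.
- Unrestricted random order at n = 26: about 4% on average, and about 9% for the worst contrast.

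**8. Balance without the term.** With Williams sequences and no position factor, drift still inflates the estimated error. Simulated type I error at n = 24 with the same total drift was 0.037, so the test is conservative.

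**The case against.** The strongest reply is that randomised order with a repeated-measures ANOVA is conventional and valid, and that the losses above rest on drift the documents do not show. Much of this stands:

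- **Scheme not stated.** A reader might infer that order is drawn independently and without balance for each participant. The article says only that it is randomised, and a Latin-square list would fit that wording. The scheme may also be in the full protocol. The figures for unrestricted random order are therefore conditional.
- **No bias.** A reader might infer that chance imbalance in position biases the contrasts. It does not. Random order keeps them unbiased, and the imbalance is already counted in the variance of 7.0.
- **Exposure.** A reader might take Table 3 to mean five hours of effort, half of it maximal jumping. The budget includes rest, the locomotion is about an hour of movement, and most hops in the ramp are below maximal height.
- **Mitigation.** The familiarisation visit at all six levels, the warm-up, the gaps between jumps and self-selected rest should all reduce drift. They do not remove it. Familiarisation covers three of the ten locomotion trials and uses submaximal hops and countermovement jumps, and the T1 warm-up is submaximal at 1g.
- **Limits of the remedy.** Since 26 is not a multiple of six, balance is only near-exact, and data loss would disturb it further. A position term removes average drift, not drift that differs between people.

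None of this changes the fact that the stated models leave out position. That is what the analysis section fixes, not a detail left unsaid.

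**Conclusion.** The point holds as a loss of precision that can be avoided at very little cost. The stated ANOVAs contain no position term, so average drift stays in the error. If order is unrestricted random, contrast variance rises by about 3%, 12% or 28% at the assumed drifts. At alpha 0.05 and n = 21, power falls from 0.95 to between 0.944 and 0.890. The loss is larger for contrasts corrected over 15 pairs. If the order proves to be balanced, the position term is still needed, because otherwise the estimated error is too large.

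The size depends wholly on the assumed drift and SD. With little drift, little is lost. The documents support neither a claim of bias nor one of an invalid test.

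**What to change.** Make two changes together:

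1. Assign gravity order at random from the six sequences of a 6 x 6 Williams square. Among 26 participants, four sequences are used four times and two are used five times. This balances position and immediate predecessor almost exactly. Keep the random order of trials within each gravity block, and state the scheme in the protocol.
2. Add gravity-block position (1–6) as a fixed effect in the gravity analyses, for example through a linear mixed model with participant as a random effect. State whether locomotion and plyometric trials share a gravity block. If they are run as separate passes, use the position within each pass.

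The cost is a different randomisation list, 5 error degrees of freedom (125 to 120 in the one-way model) and about 0.2% of contrast variance. No participants or time are added. The six-level position term without balanced sequences would cost about 4%, more than the 3% it recovers at 1% drift per block, which is why the two changes belong together. If orders have already been drawn without balance, a single linear position term is the cheaper choice, at about 0.8% of contrast variance at n = 26.
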